##### Cost-effectiveness analysis

Using the data collected from performance center coordinators, a *cost analysis* will first be conducted to identify and measure the direct, tangible costs of the resources used in administration and implementation of the F3HK program. This analysis will be done from both the program perspective and the broader societal perspective. Analysis from the program perspective will focus on costs directly incurred during preparation for and implementation of the various components of the F3HK program, including the monetary value of in-kind contributions. Analysis from the societal perspective will estimate all costs incurred and health effects obtained as a result of the program, including estimation of costs and effects experienced beyond the participant and program perspectives [100].

A preliminary *cost-effectiveness analysis* (CEA) then will be completed, which will build on the cost analyses conducted from the broader societal perspective and will include opportunity costs experienced by participants (i.e. time at CSA site or education class that could have been used in other valued ways). We will use the human capital method and value participants’ time based on wage rates [101]. We will estimate the value of participants’ time using income data collected from participant questionnaires and national average wage rates from the Bureau of Labor Statistics [102]. An incremental cost-effectiveness ratio (ICER) will be calculated by (1) subtracting the cost of the F3HK program (as determined by the cost analysis) from the cost of the alternative (no program, $0); (2) subtracting the change in fruit and vegetable intake from baseline to late-season in the control group from the change in fruit and vegetable intake during that same interval in the intervention group, as measured by the FVS; and (3) dividing the program cost by the difference in the change in fruit and vegetable intake between the control and intervention groups. This ratio will thus provide an estimate of the program cost per unit change in fruit and vegetable intake. Epidemiologic data will be used to estimate the impact of changes in fruit and vegetable intake on life expectancy and quality, or Quality Adjusted Life Years (QALYs) [101], which will allow for a comparison of cost-effectiveness between F3HK and other programs aimed at improving the public’s health.

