Nutrition assistance and education participation (household)	**X**	**X**	**X**
Physical activity and sedentary behavior measures (child)	**X**	**X**	**X**
General health status (caregiver and child)	**X**	**X**	**X**
Costs associated with food purchasing and preparation (household)	**X**	**X**	**X**
Costs associated with CO-CSA participation (household)		**X** ^**a**^	
Kitchen inventory (household)	**X**		
Household composition and demographics	**X**	**X**	**X**
CSA participation (outside of/in addition to the research study; household)	**X**	**X**	**X**
	Year 2	Year 3	Year 4
Process evaluation			
Program evaluation			
Dose delivered	**X**	**X**	**X**
Dose received	**X**	**X**	
Fidelity	**X**	**X**	
Experiences	**X**	**X**	
Program cost	**X**		
Non-participation	**X**		

^a^Subset of participants

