**Costs associated with food purchasing and preparation.** Caregivers will be asked 12 questions to assess (1) cooking supply costs; (2) grocery shopping expenses; (3) time and travel costs associated with shopping at the grocery store; (4) time spent planning meals; (5) time spent cooking meals; and (6) any costs associated with “eating out” or purchasing prepared meals and snacks not included in the reported grocery costs.

**Costs associated with CO-CSA participation (specified assessments only).** Costs associated with CO-CSA participation, including the time and financial costs associated with program participation and related food preparation behaviors, will be assessed in the fall each year the household is assigned to receive the CO-CSA. Questions will cover (1) employment and wages; (2) costs associated with travel to and from the CSA pick-up site and the F3HK healthy eating classes, including childcare costs, if applicable; (3) time spent at the pick-up site and healthy eating classes; and (4) the value of contributions to program success (e.g. volunteered time or donated supplies). Questions pertaining to the healthy eating classes will be asked only in the years and to the groups that the classes are offered.

**Kitchen inventory (baseline only).** At baseline, caregivers will be asked about ownership of 14 common kitchen implements (paring knife, chef’s knife, cutting board, spatula, cooking spoons, vegetable peeler, salad spinner, mixing bowl, frying/sauté pan, storage container, saucepan, colander, slow cooker, and food processor), how commonly they are used to prepare, cook, and store fresh fruit and vegetables, and their quality. For those that they do not own, caregivers will be asked which would make preparing, cooking, and storing fresh fruit and vegetables easier.

**Household composition and demographics.** At baseline, all adult participants will compete questions drawn from the American Community Survey [95] and BRFSS [96] about household composition (age, gender, and relationship of all household members) and demographic characteristics (race/ethnicity, education, employment, and household income). Questions and response options will be modified to an online format and simplified, where needed. Adult participants also will report whether anyone in the household smokes. Caregivers will be asked to provide the name, age, and gender of the focal child and the number of days in a typical week that he or she lives with the respondent.

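### The cost-effectiveness ratio claims a societal perspective, but its numerator is gross program cost against a $0 comparator (with the subtraction also written backwards in step 1), so changes in household food and time costs, measured in both arms, are left out

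*Protocol article*

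**What the plan says.** The protocol article, under Cost-effectiveness analysis, describes a cost analysis from a program and a societal perspective, followed by a preliminary cost-effectiveness analysis. On scope it states: "Analysis from the societal perspective will estimate all costs incurred and health effects obtained as a result of the program". The cost-effectiveness analysis is one "which will build on the cost analyses conducted from the broader societal perspective", with participants' opportunity costs for time at the pick-up site or in class included.

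The ratio is then fixed in three steps:

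- Step 1 sets the cost difference by "subtracting the cost of the F3HK program (as determined by the cost analysis) from the cost of the alternative (no program, $0".
- Step 2 sets the effect difference, on the fruit and vegetable screener and with the intervention group as the arm subtracted from, by "subtracting the change in fruit and vegetable intake from baseline to late-season in the control group from the change in fruit and vegetable intake".
- Step 3 forms the ratio by "dividing the program cost by the difference in the change in fruit and vegetable intake between the control and intervention groups".

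The section closes the definition with "This ratio will thus provide an estimate of the program cost per unit change in fruit and vegetable intake".

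The Program cost assessment paragraph, under Process evaluation, says how the resource total is formed: program administration costs combined with the data on costs of CO-CSA participation. It names no other source.

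A separate household module exists. Under Online questionnaires: "Caregivers will be asked 12 questions to assess (1) cooking supply costs; (2) grocery shopping expenses", followed by shopping time and travel, meal planning time, cooking time, and eating out or prepared food. Table 5 schedules "Costs associated with food purchasing and preparation (household") at baseline, fall and spring, with no subset footnote. The CO-CSA participation cost row does carry that footnote, and is asked in the fall only. The design text for Component 4 says all participants are assessed at the same time points.

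**The concern.** There are two separate faults. First, the cost difference in step 1 runs control minus intervention while the effect difference in step 2 runs intervention minus control, and step 3 does not use what step 1 produces. An analyst cannot follow all three steps as written.

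Second, zero is what the absence of a program costs the program. It is not what a control household costs society over a season: that household buys groceries, eats out, shops and cooks. What matters for an incremental ratio is how far the program changes those costs. The protocol's own Background gives reason to expect some change, since it cites reports that shares can be cheaper than equivalent store produce and that members eat at home more and out less.

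At stake is what the ratio can be said to measure. The effect in the denominator comes from a randomized comparison, whereas the numerator is an uncontrolled gross cost. The section then plans to compare F3HK with other public health programs on cost-effectiveness using QALYs. A gross program cost presented as societal does not support that comparison.

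**Working it through.** **Inputs**

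- C, program cost per household: the document gives none. Assumed values of $500 and $1,000.
- E, between-arm difference in intake change: one-third of a serving per day, from Sample size calculations. That is the difference the trial is sized to detect, used here only for illustration.
- D, between-arm difference (intervention minus control) in household food and time costs: the document gives none. Assumed range of -$300 to +$150, so that net savings and net extra cost are both covered.

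The plan states no cost and no ratio, so there is no figure to reproduce.

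**Check 1: the direction of the subtraction**

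- Step 1 as written: 0 - C = -C.
- Step 2 as written: intervention change minus control change = E.
- Step 1 carried into the ratio: -C/E. With C = $500: -500/(1/3) = -$1,500 per serving per day. With C = $1,000: -$3,000.
- Step 3 as written: +C/E, which gives +$1,500 and +$3,000.

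Steps 1 and 3 disagree in sign. Step 3 and the sentence after it fix the reported quantity as +C/E.

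**Check 2: the $0 comparator**

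Write household food and time cost as H in each arm.

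- Societal cost, intervention: C + H(intervention).
- Societal cost, control: 0 + H(control).
- Difference: C + [H(intervention) - H(control)] = C + D.

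The planned numerator, C, equals this only if D = 0. The societal ratio is (C + D)/E, which is (C + D)/C times the planned one:

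| C (assumed) | D (assumed) | C + D | (C + D)/E | Relative to C/E |
|---|---|---|---|---|
| $500 | -$300 | $200 | $600 | 0.40 |
| $500 | -$150 | $350 | $1,050 | 0.70 |
| $500 | $0 | $500 | $1,500 | 1.00 |
| $500 | +$150 | $650 | $1,950 | 1.30 |
| $1,000 | -$300 | $700 | $2,100 | 0.70 |
| $1,000 | -$150 | $850 | $2,550 | 0.85 |
| $1,000 | $0 | $1,000 | $3,000 | 1.00 |
| $1,000 | +$150 | $1,150 | $3,450 | 1.15 |

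**Check 3: does D enter anywhere in the plan?**

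- Program cost assessment forms the total from administration and CO-CSA participation costs only.
- Cost-effectiveness analysis adds opportunity cost, with time at the site or in class as its example.
- Neither text refers to the food purchasing and preparation module.
- The CO-CSA participation module is asked only of households assigned to the CO-CSA that year, so it has no control counterpart and cannot yield D.

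**Check 4: can D be estimated?**

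Yes. The household module is asked at baseline and fall in both arms, which matches the baseline to late-season interval used for the effect.

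**The case against.** The best defence is that C is not a bare program cost. It is taken from the cost analysis, whose societal version is said to cover all costs that result from the program. On that reading C is already net of what would have happened without the program, $0 is the matching reference, and ordinary grocery spending in control households is rightly ignored. The CO-CSA module also asks about food preparation behaviors linked to participation, so the household side is not wholly absent.

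Part of this stands. Only a change caused by the program matters, not the level of control spending, and the societal definition does not exclude such a change. What defeats the defence is the one place where the total is assembled: it draws on administration and participation costs, neither of which contains a contrast with control households. A condensed article may leave the allocation of cost items to a fuller document, but this one fixes the comparator value, the numerator and the sources of the total.

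Two further points on that side hold. The analysis is labelled preliminary and is not among the outcomes in Table 4, so no dietary result depends on it. And a reader might infer from step 1 that the published ratio would carry the wrong sign; the documents do not support that, because step 3 puts the positive program cost in the numerator.

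**Conclusion.** The point holds in two parts of unequal weight. The reversed subtraction in step 1 is a wording error that contradicts step 3 and would probably not reach the reported figure. The mismatch between the claimed societal perspective and a gross-cost numerator against $0 is substantive: as written, the ratio is program and participation cost per unit of intake, not an incremental societal cost.

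The size and direction of the error are unknown. The factors of 0.4 to 1.3 (C = $500) and 0.7 to 1.15 (C = $1,000) rest wholly on assumed costs and show only that the effect could be material either way. A reader might infer that the ratio must be overstated because a share replaces groceries. The documents do not establish that, since extra cooking time or spending could offset any saving. A reader might also infer that a trial-wide cost will be divided by a per-participant effect; the text is merely silent on scaling. Nor is the conversion of intake change into QALYs itself at fault: only the cost side of the later comparison is affected.

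The economic conclusions should be corrected before analysis. The dietary outcomes are untouched.

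**What to change.** - Rewrite step 1 as intervention minus control. Incremental cost = program and CO-CSA participation cost per intervention household, plus the between-arm difference in household food purchasing, eating-out, shopping, planning and cooking costs, over the same baseline to late-season interval as the effect.
- State how double counting is avoided, in particular for share payments that may also appear as grocery spending, and for time recorded in both cost modules.
- Use this incremental cost as the numerator in step 3, divided by the between-arm difference in intake change.
- Keep the ratio based on program cost alone as a second result, labelled program-perspective.

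The cost is a few lines of text and some added analysis of data already scheduled for collection. The drawback is that the household cost difference carries sampling error, so the societal ratio will be less precise than one built on a fixed program cost. If the sponsor does not want that analysis, the minimum is to correct step 1 and drop the societal label from the ratio.

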### Component 5: Economic impact on farmers and communities

#### Data collection and outcomes

We will assess the economic impact of the CO-CSA program at the farm level and at the community level. Measuring the profitability of CSA programs for farmers is complex [39, 40, 44, 47], and measuring the economic impact of a cost offset modification to farmers’ CSA programs presents additional challenges, as CO-CSA participants likely represent a small sub-section of the CSA membership of each farm. We will measure the economic outcomes of the CO-CSA for farms using in-depth interviews with farmers participating in the randomized trial (component 4). The questions in the interview guide will be used to assess the economic impact of adding cost offset shares to the farmers’ CSA. These questions will mostly be qualitative and will focus on changes to revenue stream, changes to profitability, impact on consumer base, and changes implemented on the farm (e.g. changes to the distribution model, acceptance of SNAP benefits, produce grown).

To estimate the economic impact of CO-CSA programs on local communities, we will use the input-output economic model (IMPLAN) and augment it with additional contextual data. While IMPLAN is one of the most commonly used models to conduct economic impact studies, researchers have found that the model does not fully capture the impacts of smaller, diversified farms and other small-to-medium scale operations that frequently participate in the localized food system [103–105]. Often, farmers selling to local and regional markets spend more money locally and spend it differently than “average” farms in the agricultural sector [106]. As a result, the economic impact of these farmers is different that the impact of the default agricultural sector in IMPLAN. To address the limitations of the default IMPLAN agricultural sector, we will customize the model using quantitative data collected from the participating farms at the time of the in-depth interviews. Questions will focus on producers’ annual sales, payroll, number of employees, operating expenses, and expenditure patterns such as input and services purchased and location of these purchases.

#### Economic analysis

Interviews with farmers will be conducted by trained study personnel at the end of Year 2 and will be audio-recorded and transcribed verbatim. The economic analysis will be conducted in two steps. First, qualitative data related to economic impact of the CO-CSA program at the farm level will be coded and analyzed using the content analysis approach [107] with the support of qualitative data analysis software. Second, economic data collected from farmers will be used to create a CSA farm sector in IMPLAN following procedures recommended in a recent USDA toolkit on assessing the economic impact of local food system initiatives [49]. We will extrapolate the CSA farm sector in each state using the data collected from farmers and the number of farms that have a CSA program based data from the 2012 Census of Agriculture. Once the CSA farm sector in IMPLAN has been created, we will calculate potential economic effect in each state under various scenarios such as the current economic contribution of the CSA farms to the state economies and the potential economic impact of the CSA farms sectors to state economies if the number of low-income participants increase through CO-CSA programs.

### Component 6: Develop business plans for long-term sustainability of CO-CSAs

Expanding markets to include low income families in a sustainable manner, without loss of profitability, is a key goal of this project. The research team will support this effort by (1) offering CSA farmers online resources informed by formative evaluation (component 1); (2) holding regular interactive webinars and online chats for farmers participating in the randomized trial (component 4) for peer-to-peer networking and problem-solving; and (3) convening the advisory group of agribusiness experts to provide technical assistance, provide feedback as the online resources are being developed, and host webinars or chats.

Beginning in Year 2, we will host chat sessions for farmers participating in component 4 (randomized trial) that will allow them to share experiences, discuss challenges, and brainstorm solutions in real time as they are implementing the first year of the F3HK program. Notes from these chat sessions will be incorporated with formative evaluation (component 1) results at the end of each season in order to inform improvements to component 4 (randomized trial).

We will also develop a toolkit with business support tools and resources based on findings from components 1, 2, and 5 (formative evaluation, longitudinal analysis, and economic analysis), along with an environmental scan of online resources. The toolkit will include a menu of strategies for subsidizing 50% of cost-offset shares. Possible strategies include having full-price members pay extra to cover the subsidy; grants from government agencies, businesses, or non-profits; community fundraisers (e.g. harvest dinners); or a combination of these approaches. The toolkit will include a summary of findings concerning the cost threshold full-price CSA members are willing to pay to subsidize others. The tool kit will be disseminated online through the project website, through cooperative extension and other appropriate channels beginning in Year 3.

The toolkit will support farmers participating in the randomized trial (component 4) as they begin developing business plans that will allow them to sustain the CO-CSA program in a manner which best suits their local context. Development of long term plans also will be supported by trainings that occur as part of an annual interactive webinar featuring extension agents, agripreneurs, and others with expertise in running CO-CSAs, to be held in Years 3 and 4. This component will be evaluated through online questionnaires and capture data related to overall reach. We will work with project partners to disseminate webinars.

### Component 7: Develop student education modules related to food systems and obesity prevention

An important component of the USDA’s Agriculture and Food Research Initiative (AFRI) call which funded this project is the inclusion of training opportunities for the “next generation of educators and scientists” in the area of childhood obesity and food systems research. While some instructional materials exist which relate to the potential benefits and desirability of food systems approaches to addressing health promotion for consumers and economic opportunities for farmers, there is a dearth of teaching materials that synthesize the emerging evidence of impact on both consumers (health) and producers (economic opportunity). To contribute to this relatively new area of teaching in higher education, we will conduct a review of the literature as well as existing instructional materials to determine important content area and what is currently addressed. Informed by this work, we will develop and disseminate materials for undergraduate and graduate level training that will assist course instructors with teaching evidence-based intervention strategies and research methods. This will include a case study approach, creating original modules to highlight relevant research projects that illustrate some of the challenges and opportunities that will likely be faced by emerging researchers and educators focusing on the nexus of childhood obesity and sustainable food systems.

### Dissemination

A committee has been established to review and approve all study dissemination materials, defined as abstracts, posters, manuscripts, and other products intended for internal or external dissemination that include data or descriptions of processes from work conducted as part of the project (Additional file 3). Authorship will be determined in line with the guidelines of the International Committee of Medical Journal Editors [108]. Datasets for this project will be made available on reasonable request.

## Discussion

Important disparities in diets and nutrition-related disease persist. Socioeconomically disadvantaged groups have lower intake of fruit and vegetables [15, 21, 22] and poorer diet quality [109], as well as higher risk of overweight, obesity, and a number of other chronic health conditions [7, 19]. Establishing healthy behaviors at an early age is important since they track between childhood and adulthood [110]. Dietary behaviors are determined by diverse environmental and individual factors, including access to acceptable nutritious foods and nutrition knowledge, attitudes, and beliefs. Approaches that address multiple constraints to healthy eating faced by children from poor families are needed in order to more effectively reduce current and future health disparities.

This integrated and innovative project has the potential to address some of the underlying determinants of poor diets among socioeconomically disadvantaged groups and, in so doing, positively affect fruit and vegetable intake, weight maintenance, and local agricultural economies. It will contribute new evidence about how local foods initiatives can more effectively meet the needs of low-income households and will produce information and resources that will help farmers and public health advocates across the nation develop and sustain CO-CSA programs while training the next generation of researchers.

